### Microbiological analysis

2.7

Quantification of the total number of bacteria and 26 pathogens will be performed by real-time PCR. The pathogens selected periodontal or carious bacteria: *Actinomyces odontolyticus, Aggregatibacter actinomycetemcomitans, Bifidobacterium dentium, Campylobacter rectus, Campylobacter gracilis, Capnocytophaga ochracea, Clostridium cluster IV, Clostridium cluster XIV, Eikenella corrodens, Fusobacterium nucleatum, Lactobacillus* spp.*, Parvimonas micra, Porphyromonas gingivalis, Prevotella intermedia, Prevotella nigrescens, Rothia dentocariosa, Scardovia wiggsiae, Streptococcus cristatus, Streptococcus mitis, Streptococcus mutans, Streptococcus salivarius, Streptococcus sanguinis, Streptococcus sobrinus, Tannerella forsythia, Treponema denticola,* and *Veillonella parvula.* Simplex quantitative real-time PCR assays will be performed in a volume of 10 μL (2 μL of DNA extract, 1 × SYBR® Premix Ex TaqTM Tli RNaseH Plus and 1 μM of each primer) (TaKaRa, Shiga, Japan).

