#### Sample size

2.8.1

With an alpha error of 5% (2-sided test), a power of 80%, an intraclass correlation coefficient of 0.8 and a mean difference of bacteria counts between the two caries risk groups of 1,300,000, a total of 200 sites, meaning 50 subjects, needs to be selected.

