#### Analysis

2.8.2

Three main steps will be realized: preparation of descriptive summaries, modelling using a mixed (linear) model and correlating bacterial abundances. A mixed linear model for the log-count abundance of each species at a measured site will be used to test for potential effects of gender, interdental space and the location of each site. Two categorical variables (site location and gender), and one numerical variable (interdental space) will be modelled as fixed effects and one categorical variable will be modelled as a random effect (subject). This random effect will be included to model correlation between the four interdental sites of a given study participant. In the regression, each coefficient will be tested according to the null hypothesis which indicates that the coefficient is zero when a likelihood-ratio test is applied. The p-values less than 0.001, 0.05, and 0.01 will be respectively considered strong, medium and low evidence with respect to the null hypothesis. To perform the correlation analysis and avoid over-estimating the inter-site correlation, the residuals of the model described above will be used. The trees associated with the correlation plot will be generated by hierarchical cluster analysis with complete linkage. Other multivariate analyses, such as factor analysis, will be used to graphically check the correlations between bacteria quantification and all potential caries risk factors. A multilevel logistic regression analysis will finally be performed to test which oral characteristics are significantly linked with the two caries risk groups. The linear mixed effects modelling package, lme4 [21] in R environment [22] will be used to generate all statistical analyses and associated plots.

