Thus, the MIARC trial allows one to evaluate if carious pathogens are present in the interdental space of adolescents and to determine if the interdental microbiota of adolescents with a high carious risk is different from the one of adolescents with a low carious risk. This should allow one to determine a specific biomarker of each carious risk. This quantification of determined bacteria could be added to CRA to improve them. This study should help optimize recommendations in terms of oral prevention in this at-risk age group. Furthermore, the expected results will provide new information on the association between the level of carious risk, measurement of the state of oral hygiene, clinical signs of gingival inflammation, diameter of the interdental spaces and interdental microbiota composition.

In conclusion, the MIARC study is a first step before further studies, ideally longitudinal clinical studies encompassing large populations which would identify the panel of bacteria as prospective oral health markers. With this new data, oral health professionals will be able to collect and analyse interdental microbiota to prevent the risk of new caries.

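### Raw p-value cut-offs are fixed for 26 species models and nothing controls error in the search for a caries-risk biomarker

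*Protocol article*

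**What the plan says.** All references are to the protocol article.

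- **Panel (2.7 Microbiological analysis):** "Quantification of the total number of bacteria and 26 pathogens will be performed by real-time PCR".
- **Species models (2.8.2 Analysis):** "A mixed linear model for the log-count abundance of each species at a measured site will be used to test for potential effects of gender", and also of interdental space and site location. The terms are listed: "Two categorical variables (site location and gender), and one numerical variable (interdental space) will be modelled as fixed effects", with subject as the random effect. Caries-risk group is not in the list.
- **Unit of testing (2.8.2):** "each coefficient will be tested according to the null hypothesis which indicates that the coefficient is zero when a likelihood-ratio test is applied".
- **Cut-offs (2.8.2):** "The p-values less than 0.001, 0.05, and 0.01 will be respectively considered strong, medium and low evidence with respect to the null hypothesis".
- **Risk-group analysis (2.8.2):** "A multilevel logistic regression analysis will finally be performed to test which oral characteristics are significantly linked with the two caries risk groups". The predictors, the number of tests and the significance level are not given.
- **Sample size (2.8.1):** "With an alpha error of 5% (2-sided test), a power of 80%, an intraclass correlation coefficient of 0.8", for one difference in bacteria counts between the two risk groups, giving 200 sites or 50 subjects.
- **Purpose (3 Discussion):** "This should allow one to determine a specific biomarker of each carious risk". The same paragraph says that the quantified bacteria could be added to caries risk assessment tools.

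**The concern.** The article sets a decision rule: which models are fitted, that every coefficient is tested, and which p-values count as evidence. The rule is applied species by species to 26 taxa. No outcome is singled out and no allowance is made for the number of tests. The logistic regression, the only stated test that involves risk group, has no error control either. The sample size rests on a single 5% test.

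The study exists to nominate bacteria for a risk tool. If species are picked because they pass a raw 0.05 cut-off, one or more hits would be an ordinary result even when the two risk groups do not differ. A reader could not tell such a list from a real signal.

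**Working it through.** **The plan's own figure.** Section 2.8.1 gives 200 sites (50 subjects) for one two-sided 5% comparison with 80% power, intraclass correlation 0.8 and a difference of 1,300,000. With four sites per subject the design effect is 1 + (4 − 1) × 0.8 = 3.4, so 200 / 3.4 = 58.8 effective sites, or 29.4 per group. No standard deviation is given, so the figure cannot be reproduced. Solving backwards, SD = 1,300,000 / [(1.960 + 0.842) × √(2 / 29.4)] ≈ 1.78 million. The calculation covers one comparison, and the article states no error rate for the panel.

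**A. Tests that section 2.8.2 sets out**

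Inputs: 26 species (2.7) and three fixed-effect factors (2.8.2). Four site locations are assumed, matching the four sampled sites in 2.6.

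- By factor: 3 × 26 = 78 tests. Expected false results at 0.05 if no effect is real: 78 × 0.05 = 3.9.
- By coefficient: (3 location + 1 gender + 1 space) × 26 = 130 tests. Expected: 130 × 0.05 = 6.5.
- Chance of at least one, if independent: 1 − 0.95^78 = 98.2%; 1 − 0.95^130 = 99.9%.

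These would be false gender, space or location effects.

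**B. Tests that the biomarker aim implies**

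Assumption: one risk-group test per species. The article does not set this family out.

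- Expected false positives at 0.05 under no true difference: 26 × 0.05 = 1.3, whatever the correlation between species.
- Chance of at least one, if independent: 1 − 0.95^26 = 73.6%. If total bacteria is tested as well, 1 − 0.95^27 = 75.0%.
- At the other stated cut-offs, if independent: 1 − 0.99^26 = 23.0% at 0.01; 1 − 0.999^26 = 2.6% at 0.001.

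**C. Sensitivity to correlation between species**

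For two-sided normal test statistics with common correlation r and c = 1.96, the chance of at least one false positive is 1 − E{[Φ((c − √r·x)/√(1 − r)) − Φ((−c − √r·x)/√(1 − r))]^26}, with x standard normal.

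| r | 26 tests at 0.05 | 26 tests at 0.01 |
|---|---|---|
| 0 | 73.6% | 23.0% |
| 0.2 | 67.6% | 20.8% |
| 0.4 | 55.0% | 16.5% |
| 0.5 | 47.5% | 14.1% |
| 0.8 | 24.5% | 6.8% |

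At 0.05 the chance passes below one half between r = 0.4 and r = 0.5.

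**The case against.** A reader might infer that the quoted coefficient tests themselves select the biomarkers, so that at least one false biomarker is more likely than not. The article does not support this, for three reasons.

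- **The models contain no risk-group term.** A chance finding there is a false gender, space or location effect. The biomarker sentence is in the Discussion, and nothing ties it to those tests. The 74% belongs to a family of tests that the aim implies but section 2.8.2 does not write down.
- **0.05 is not the only cut-off.** It is one of three grades. This cuts both ways: as printed, p below 0.05 is medium evidence and p below 0.01 is low, so the two labels look transposed. Taken literally, 0.05 carries more weight than 0.01.
- **Independence is an upper case.** Section 2.8.2 itself plans to study correlation between species, and at r = 0.5 the chance is already just under one half.

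Two further points are fair. Testing location by coefficient is only one reading, since a likelihood-ratio test can take the whole factor at once; hence both counts above. The Discussion also calls the study a first step before longitudinal work, which argues against strict family-wise control.

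The strongest general defence is that a condensed article may leave multiplicity to an analysis plan that is not shown. That would settle the matter if section 2.8.2 were silent. It is not: it states the unit of testing and the cut-offs. An unseen plan that adjusts p-values would depart from the printed rule, and the two would need reconciling.

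**Conclusion.** The point holds in a conditional form. Unadjusted cut-offs are fixed for 26 species models, the risk-group regression has no stated error control, and biomarkers are expected from the same panel.

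The tests as written would give 3.9 (by factor) or 6.5 (by coefficient) false results at 0.05 if no effect were real, none of them about caries risk. Risk-group comparisons for every species at 0.05 would give 1.3 expected false positives. The chance of at least one would be up to about 74%, about 48% at a correlation of 0.5 and about 24% at 0.8, or 23% at a 0.01 cut-off with independence. These figures assume that no species differs between groups and that each species has one risk-group test.

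The article does not show that a false biomarker is more likely than not. This should be put right before analysis. It does not undermine the data to be collected.

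**What to change.** 1. Add caries-risk group as a fixed effect in each of the 26 species models. Without it there are no risk-group p-values to adjust.
2. Apply Benjamini-Hochberg at a 5% false discovery rate to those 26 p-values, and call a species a candidate biomarker only if its adjusted p is below 0.05. This suits a first-step study better than Bonferroni, whose per-test level would be 0.05 / 26 = 0.0019.
3. Name one lead risk-group comparison at 5% for the outcome behind the sample size. Section 2.8.1 says only bacteria counts; that this means total bacteria is an assumption for the sponsor to confirm.
4. Test site location with one 3-df likelihood-ratio test per species (four sites).
5. Label the other coefficients descriptive, and correct the order of the evidence labels.

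**Cost:** one extra term in each model, one adjustment step and a few sentences, with no new data. The downside is that fewer species will reach significance. How much power is lost cannot be worked out, because section 2.8.1 gives no standard deviation.

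### The cut-offs for medium and low evidence are transposed (0.05 and 0.01), so the p-value labels in the mixed-model analysis do not follow the order of the p-values

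*Protocol article*

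**What the plan says.** Section 2.8.2 of the protocol article describes a linear mixed model for the log-count abundance of each species at a site. The fixed effects are site location, gender and interdental space, and subject is a random effect. The testing rule is that "each coefficient will be tested according to the null hypothesis which indicates that the coefficient is zero when a likelihood-ratio test is applied". The next sentence sets the grading scale: "The p-values less than 0.001, 0.05, and 0.01 will be respectively considered strong, medium and low evidence with respect to the null hypothesis".

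This is the only numerical p-value criterion in the analysis section. No other part of the article restates or corrects it. The multilevel logistic regression described at the end of the same section, which relates oral characteristics to the two caries risk groups, speaks of significant links but gives no cut-off of its own.

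**The concern.** A smaller p-value is stronger evidence against the null hypothesis, so a three-tier scale should run 0.001, 0.01, 0.05 from strongest to weakest. The article runs 0.001, 0.05, 0.01, and its respective pairing leaves no doubt about which label goes with which cut-off. The last two tiers are therefore out of order.

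What is at stake is how the results are described. The labels would be attached to several coefficients in each of many models, since section 2.7 lists 26 species or groups. Applied as written, they would describe some results as weaker than others that have larger p-values. A published rule that cannot sensibly be followed as written also leaves the labelling to be settled by whoever writes the report, possibly after the results are known.

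**Working it through.** No sample-size or power formula bears on this point. The check is to apply the stated scale to a range of p-values and see whether the label ever strengthens as p rises.

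**Inputs (section 2.8.2).** Stated pairing: p<0.001 strong; p<0.05 medium; p<0.01 low. Monotone pairing for comparison: p<0.001 strong; p<0.01 medium; p<0.05 low.

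**Two ways to apply the stated scale.** The cut-offs are nested: any p below 0.01 is also below 0.05. The article does not say which label wins when a result passes more than one, so both conventions were tried.

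- Convention A: the label of the smallest cut-off passed.
- Convention B: the strongest label among all cut-offs passed.

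| p | Stated cut-offs passed | Stated scale, A | Stated scale, B | Monotone scale (A and B agree) |
|---|---|---|---|---|
| 0.0005 | 0.001, 0.01, 0.05 | strong | strong | strong |
| 0.003 | 0.01, 0.05 | low | medium | medium |
| 0.005 | 0.01, 0.05 | low | medium | medium |
| 0.009 | 0.01, 0.05 | low | medium | medium |
| 0.012 | 0.05 | medium | medium | low |
| 0.03 | 0.05 | medium | medium | low |
| 0.049 | 0.05 | medium | medium | low |
| 0.06 | none | none | none | none |

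**Result under A.** As p rises, the labels run strong, low, medium, none. Results with 0.001 ≤ p < 0.01 are graded below results with 0.01 ≤ p < 0.05.

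**Result under B.** The labels run strong, medium, none. Every p<0.05 is at least medium, so the low tier is empty and three tiers become two.

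**Direction of evidence.** The sentence does not say whether the evidence is for or against the null hypothesis. This does not help. Under A, the sequence strong, low, medium is out of order in either direction.

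**After the correction.** With 0.01 and 0.05 exchanged, p=0.005 is medium and p=0.03 is low, and the label never strengthens as p rises. Both conventions then give the same label for every p. The overlap of the tiers is therefore not a separate defect; it causes trouble only because two cut-offs are out of order.

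**The case against.** The strongest reply is that this is an obvious slip. The strong tier is right, 0.05 and 0.01 have simply changed places, and an analyst would probably correct it without thinking. Any p-value printed beside its label would show the true order. No model, test, estimate or sample size depends on the sentence. All of that stands, and it is why the point is minor. It does not make the sentence correct: the article states the rule outright, so this is not a detail left to a fuller plan.

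Three stronger readings are tempting, and the article does not support them.

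- *That candidate caries biomarkers would be ranked in the wrong order.* The scale follows directly on the tests in the species-level mixed model, and caries risk group is not among that model's fixed effects. The link with risk group is examined in the logistic regression, for which the scale is not stated. The ranking of biomarkers would be affected only if the same labels were carried over to that step, and the article does not say that they will be.
- *That the share of mislabelled results can be worked out from the planned power.* The sample-size statement in section 2.8.1 concerns "an intraclass correlation coefficient of 0.8 and a mean difference of bacteria counts between the two caries risk groups of 1,300,000". That is a contrast between risk groups on the count scale. The graded tests concern gender, site location and interdental space on the log scale, and the article gives no expected effect for any of these. The share of results falling in the two affected bands therefore cannot be derived.
- *That the scale contradicts the significance level of the design.* Section 2.8.1 begins "With an alpha error of 5% (2-sided test), a power of 80" per cent. That alpha is an input to the sample size and sets no evidence labels. Under the scale as written, every p<0.05 still receives some label, so the two sections do not conflict.

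**Conclusion.** The point holds as a minor wording error. The medium and low cut-offs in section 2.8.2 are transposed. The effect is limited to the labels of results with 0.001 ≤ p < 0.05. Under the smallest-cut-off convention the two bands inside that range exchange labels. Under the strongest-label convention they share one label and the low tier disappears. Results with p<0.001 or p≥0.05 are unaffected.

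The conclusion rests only on the sentence as printed and on the principle that a smaller p-value is stronger evidence against the null hypothesis. That 0.05 and 0.01 were exchanged by accident is an inference, though the likeliest one. The finding says nothing against the mixed model, the likelihood-ratio tests or the number of subjects.

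**What to change.** Reword the sentence in section 2.8.2 so that the tiers are ordered and do not overlap: p<0.001 is strong, 0.001 to <0.01 is medium, and 0.01 to <0.05 is low evidence against the null hypothesis. Writing *against* also removes the vagueness about direction.

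The cost is one sentence. Nothing else in the design or analysis changes. The correction is best made before any result is labelled.

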### Study population

2.3

Fifty Caucasian subjects will be selected from a group of first-time volunteers. The male/female ratio will be 1.0 as well as the CRA high risk/low risk ratio in the enrolled population.

The individual eligibility criteria are (i) aged 15-17 years-old, (ii) presence of teeth (15–16, 25–26, 35–36, and 45–46), (iii) having at least 22 natural teeth, (iv) good understanding of the French language, (v) one of the parents/legal guardians accepts the study's terms and conditions and signs the informed consent form, (vi) the adolescent accepts the terms and conditions of the study and signs the informed consent form. Moreover, the eligibility of the participant depends upon the presence of all his/her four premolar-molar pairs.

The clinical interdental site inclusion criteria are: (i) interdental brushes can penetrate into the four sites analysed, (ii) absence of diastemata, (iii) no interdental caries or prosthetics restorations in the teeth surrounding the interdental sites, (iv) absence of oral inflammation and bleeding on probing (BOP) after 30 s), (v) no clinical attachment loss (CAL) > 3 mm or pocket depth (PD) > 3 mm.

The criteria for exclusion are: (i) smokers, (ii) having an immune system disorder, (iii) having any other concomitant systemic illness, (iv) taking medication, (v) had a professional prophylaxis within the 4 weeks preceding the initial examination, (vi) taken antibiotics in the past 3 months, (vii) regularly using interdental brushes and/or dental floss and/or mouthwash, (viii) having a history of periodontal disease or treatment, (ix) undertaking a course of dental or orthodontic treatment, and (x) unable to answer questions or non-cooperative.

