### Repartition of subjects according to caries risk conditions

2.4

The American Academy of Pediatric Dentistry [3] sets out criteria which will be used, with certain modifications, to classify patients according to their carious risk (Table 1). The low carious risk subjects presented Caries Protective Terms, i.e., brushing daily with fluoridated toothpaste and regular dental care, Caries Risk Indicators, i.e., socio-economic status (medium, high) and snacking (low, medium) and Clinical Indicators, i.e., less than one interproximal lesion and no enamel defects nor active white spot lesions and adequate saliva flow rate. The high carious risk subjects presented Caries Protective Terms, i.e., no daily brushing with fluoridated toothpaste and/or irregular dental care and/or Caries Risk Indicators, i.e., low socio-economic status and high snacking and/or Clinical Indicators, i.e., more than one interproximal lesion and/or active white spot lesions and/or enamel defects and/or inadequate saliva flow rate.

**Table 1 tbl1:** Adolescent caries risk assessment.

FACTORS	HIGH RISK	LOW RISK
Biological (interview)		
- Patient with low socioeconomic status	Yes	No
- Patient has >3 between meal sugar-containing snacks or beverages per day	Yes	No
Protective (interview)		
- Patient brushes teeth daily with fluoridated toothpaste	No	Yes
- Patient has regular dental care	No	Yes
Clinical Findings (International Caries Detection and Assessment System (ICDAS) and salivary tests)		
ICDAS		
- Patient has >1 interproximal lesion	Yes	No
- Patient has active white spot lesions or enamel defects	Yes	No
Salivary tests (hydration, salivary consistency, resting saliva pH, stimulated saliva flow, stimulated saliva pH and saliva buffering capacity)		
- Patient has high salivary risk	Yes	No

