### Interdental microbiota sample

2.6

Four interdental sites (15–16, 25–26, 35–36, and 45–46), free from caries (ICDAS code 0), will be assessed for each subject. The adapted interdental brush (Curaden, Kriens, Switzerland) will be determined by using a Curaprox IAP calibration probe (Curaden) [18]. Then, the isolation of each tooth selected for sampling will be performed by using sterile dental cotton rolls and a calibrated, sterile interdental brushes (IDB) will serve to remove the interdental biofilm. The IBDs containing the individual samples will be stored in sterile tubes at 4 °C for later laboratory treatment [19,20].

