## Discussion

3

To our knowledge, the MIARC trial is the first cross-sectional clinical study which analyses the interdental microbiota according to the caries risk factor**s** of adolescents aged 15–17 years.

The sampling of site-specific microbiota for analysing the molecular properties of caries needs to reflect the localised nature of this clinical disorder. A previous study has demonstrated that the proximal surfaces were the most exposed surfaces, after the occlusal surfaces to carious lesions [23]. Indeed, the risk of interproximal carious lesions is important among the high-risk adolescents, mainly due to the lack of compliance with caries-prevention programs in this group [24]. In children aged 12 years, the prevalence of interproximal caries is 39% and increases to 72% at 20–21 years [25]. Enamel lesions on the approximal surfaces among 16-year-olds account for more than 80% of all caries lesions on these surfaces, no matter whether the caries prevalence in the population is high or low [26].

Whilst no standard benchmark or criteria for evaluating a CRA's quality exists, a universal rating of the clinical examination from ‘low to high’ will be used in this study for testing the criterion validity of carious risk. The classification criteria for CRA systems were determined by combining scientific evidence and expert opinion. From these CRAs, practitioners analyse the various clinical and social factors of a patient and can thus assign a carious risk status [27]. Our study classified patients into two risk categories: low carious risk and high carious risk. There is no necessity for further preventive professional treatment for the low risk patients and they should be offered an extended follow-up [28]. For high-risk patients, preventive actions must be taken to reduce the incidence and severity of future carious lesions [28]. This individual scheduling of preventive and follow-up activity better appropriates the use of dental resources and lowers dental costs for certain individuals [28].

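### The multilevel logistic regression on caries risk group cannot be estimated as described, because the outcome is constant within subject, and no other formal test compares the risk groups

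*Protocol article*

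**What the plan says.** The last modelling step in section 2.8.2 (Analysis) reads: "A multilevel logistic regression analysis will finally be performed to test which oral characteristics are significantly linked with the two caries risk groups". The software named for all analyses is lme4 in R. The predictors are not listed.

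The outcome belongs to the person. The items in Table 1 (section 2.4) are worded per patient, and the Discussion says: "Our study classified patients into two risk categories: low carious risk and high carious risk". Section 2.3 fixes equal groups: "The male/female ratio will be 1.0 as well as the CRA high risk/low risk ratio in the enrolled population". With 50 subjects, that is 25 and 25.

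The clustering is sites within subjects. Section 2.6 states: "Four interdental sites (15–16, 25–26, 35–36, and 45–46), free from caries (ICDAS code 0), will be assessed for each subject". For the linear mixed model, section 2.8.2 says of the subject effect: "This random effect will be included to model correlation between the four interdental sites of a given study participant". No other level is described: there is one clinic and one examiner.

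The linear mixed model has gender, site location and interdental space as fixed effects. Risk group is not among them.

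**The concern.** A random-intercept logistic model learns the between-subject variance from how far outcomes agree within a subject. If the outcome is a label attached to the subject, agreement is perfect by construction. The fitted variance is then pushed towards infinity, and software stops wherever its numerical settings stop it.

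This step carries the between-group inference. The Introduction gives the association of the interdental microbiota with carious risk as the secondary outcome, section 2.8.1 sizes the study on a difference between the two risk groups, and the Discussion expects to learn whether the groups differ and to find biomarkers. The linear mixed model leaves risk group out, and the factor analysis is a graphical check. If the logistic model fails, no formal test of the group comparison is left.

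A second question concerns the predictors. Some oral characteristics measured in the study also define the groups. Table 1 has a block headed "Clinical Findings (International Caries Detection and Assessment System (ICDAS) and salivary tests", and the high-risk clinical criteria are "more than one interproximal lesion and/or active white spot lesions and/or enamel defects and/or inadequate saliva flow rate". Nothing in section 2.8.2 keeps these items out of the regression.

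**Working it through.** **Inputs.** 50 subjects, 4 sites each, 25 per group (sections 2.3, 2.6, 2.8.1); ICC 0.8, two-sided alpha 5%, power 80% (section 2.8.1).

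**The plan's own figure.** This point challenges no stated number. The 200 sites cannot be reproduced forwards because no SD is given. Working back: design effect 1 + (4 - 1) x 0.8 = 3.4; effective sites 200/3.4 = 58.8, or 29.4 per group; standardised difference (1.960 + 0.842) x sqrt(2/29.4) = 0.73. This equals an SD of about 1.78 million for the stated difference of 1.3 million. The 0.73 is used below only as a plausible effect size.

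**Step 1: intercept-only likelihood.** Each subject contributes the integral, over the random intercept, of the probability of four identical outcomes. At SD 0 the total is 200 x ln(0.5) = -138.63. As the SD grows, each subject's four outcomes become certain once the sign of the intercept is known, and the total tends to 50 x ln(0.5) = -34.66. Numerical integration in between:

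| Random-effect SD | Log-likelihood |
|---|---|
| 0 | -138.63 |
| 1 | -101.40 |
| 5 | -50.71 |
| 10 | -42.42 |
| 100 | -35.39 |
| 1000 | -34.73 |
| limit | -34.66 |

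The curve rises throughout and has no maximum.

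**Step 2: add a site-level predictor** such as a log count (simulated: group difference 0.73 SD, ICC 0.8). The profile log-likelihood still rises, from -132.49 at SD 0 to -35.29 at SD 100. The likelihood-ratio test of the predictor depends on the SD at which it is evaluated:

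- SD 1: 2 x (101.40 - 97.35) = 8.1, p = 0.004
- SD 5: 2 x (50.71 - 49.35) = 2.7, p = 0.10
- SD 100: 2 x (35.394 - 35.289) = 0.21, p = 0.65

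**Step 3: the named software.** lme4 was fitted to three simulated data sets of the same kind:

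| Quadrature points | Random-intercept SD, range over the three sets | Wald p, first set |
|---|---|---|
| 1 | 52 to 55 | 0.40 |
| 10 | 17 to 18 | 0.13 |
| 25 | 686 to 696 | 0.73 |

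The data are the same down each p column; only a software option changes.

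**Step 4: one row per subject.** With the four-site mean as predictor and n = 50, simulated type I error was 4.8% (2000 data sets) and power at 0.73 SD was 81% (1000 data sets).

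**Step 5: if the random effect were dropped.** Treating 200 sites as independent gives a type I error of 2 x [1 - Phi(1.96/sqrt(3.4))] = 28.8% for a null predictor with ICC 0.8 (simulated 28.9%).

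**Step 6: if a Table 1 clinical item were entered.** No low-risk subject can have it, so one cell is empty and the odds ratio is infinite. With 6 of 25 high-risk subjects positive against 0 of 25, Fisher's exact p is 0.022; with 10 of 25 it is 0.0006. Both follow from the definition alone.

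**The case against.** The article does not spell out the levels of the logistic model, and a fuller plan may list its predictors. The first part carries little weight: sites within subject is the only hierarchy given, and a multilevel model in lme4 leaves little other reading. The predictor list is fairly left to a fuller plan, and that limits what can be said about circularity.

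Several stronger readings are tempting, and the documents do not support them:

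- **That the regression's findings are circular as a whole.** The plan says only oral characteristics. Bacterial counts and interdental diameter are not in Table 1, and links with them would not be circular. Sampled sites must be ICDAS code 0, so a site-level ICDAS score cannot vary; only patient-level ICDAS findings, salivary results or interview items could be circular, and only if entered.
- **That separation would be complete.** The high-risk criteria are joined by and/or, so a high-risk subject may lack any one item. A single item gives quasi-separation.
- **That the plan carries a 29% false-positive rate.** That figure belongs to a workaround the plan does not propose. The model as written behaved differently in the fits above: unstable, and insensitive to a real difference.
- **That the regression is meant to establish criterion validity.** The Discussion's phrase "for testing the criterion validity of carious risk" concerns a low-to-high rating of the clinical examination and does not refer to this model.

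It can also be said that the logistic model is not among the three main steps and that the association is a secondary outcome. That is true, but the sample size rests on the group difference, so the step is not peripheral.

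**Conclusion.** The point holds for the model itself. A logistic regression with a subject random intercept and a subject-level outcome has no finite variance estimate, and its coefficients and p-values for site-level predictors would reflect numerical settings. This is an error in what is stated, since a fuller plan that carried out the sentence would meet the same problem. As a result, the study has no valid formal test of its risk-group comparison.

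The conclusion assumes that multilevel means sites within subjects. The likelihood figures assume 25 subjects per group. The predictor results use simulated data with ICC 0.8 and a 0.73 SD difference, the latter inferred from the stated sample size. The circularity is conditional: it is certain for any Table 1 item that is entered, and absent for the others.

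**What to change.** Change the wording of section 2.8.2 in one of two ways.

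1. Add risk group as a fixed effect in the existing linear mixed model of log counts. This keeps all 200 sites and the subject effect, and tests the group difference directly.
2. Or replace the multilevel logistic model with an ordinary or Firth-penalised logistic regression, one row per subject (n = 50), using four-site mean log counts for a few predictors named in advance.

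In either case, state that the Table 1 items (ICDAS findings, salivary tests, interview items) are excluded as predictors of risk group, and that the subject effect will not be dropped from a site-level logistic model to obtain a fit.

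No new data are needed. The cost of the logistic option is a nominal n of 50 in place of 200 and room for few predictors: with 25 subjects per group and 26 species, entering all species together would leave 25/26 = 0.96 events per species.
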